## Abstract

**Background:**

Improving arm-hand skill performance is a major therapeutic target in stroke rehabilitation and needs intensive and varied training. However, guided treatment time is limited. Technology can assist in the training of patients, offering a higher intensity and more variety in content. A new task-oriented arm training approach was developed, using a ‘Remote Handling concept based’ device to provide haptic feedback during the performance of daily living activities (ReHab-TOAT). This study aims to investigate the effects of ReHab-TOAT on patients’ arm-hand function and arm-hand skill performance, quality of life of both patients in the chronic phase after stroke and their caregivers and the patients’ perception regarding the usability of the intervention.

**Methods:**

A randomized clinical trial was designed. Adult chronic stroke patients suffering from hemiparesis and arm-hand problems, with an Utrechtse Arm-hand Test score of 1–3, will be invited to participate. Participants in the experimental group receive ReHab-TOAT additional to care as usual. ReHab-TOAT contains task-oriented arm training for stroke patients in combination with haptic feedback, generated by a remote handling device. They will train for 4 weeks, 3× per week, 1.5h per day. Participants in the control group will receive no additional therapy apart from care as usual. The Fugl-Meyer Assessment (FMA), measuring participants’ motor performance of the affected arm, is used as the primary outcome measure. Secondary outcome measures are arm-hand capacity of the patient (ARAT), perceived arm-hand skill performance (MAL), actual arm-hand skill performance (accelerometry), patients’ quality of life (EuoQol-5D) and caregivers’ quality of life (CarerQoL). Participants’ perception regarding the usability of the intervention, including both the developed approach and technology used, will be evaluated by the System Usability Scale and a questionnaire on the user experience of technology. Measurements will be performed at 1, 2, 3 and 4 weeks pre-intervention (baseline); immediately post-intervention; and 3, 6 and 9 months post-intervention. Statistical analysis includes linear mixed model analysis.

**Discussion:**

This study is designed to investigate the evidence regarding the effects of ReHab-TOAT on patients’ performance at different levels of the *I*nternational *C*lassification of *F*unctioning, disability and health (*ICF*) model, i.e. a framework measuring functioning and disability in relation to a health condition, and to provide insights on a successful development and research process regarding technology-assisted training in co-creation.

**Trial registration:**

Netherlands Trial Register NL9541. Registered on June 22, 2021

**Supplementary Information:**

The online version contains supplementary material available at 10.1186/s13063-023-07139-w.

## Administrative information

Note: the numbers in curly brackets in this protocol refer to SPIRIT checklist item numbers. The order of the items has been modified to group similar items (see http://www.equator-network.org/reporting-guidelines/spirit-2013-statement-defining-standard-protocol-items-for-clinical-trials/).

## Introduction

### Background and rationale

Sixty-six percent of stroke patients still experience deficits in the upper limb 6 months after stroke [1], and only 5 to 20% reach complete functional recovery of the paretic arm in terms of arm-hand skill performance (AHSP) [1, 2]. It is hypothesized that more motor therapy time and higher variability in treatment content may lead to further improvement [3, 4], which next to improved quality of life of the patient may also lead to improved quality of life of his/her caregiver, because both the amount and content of support for the patient may decrease/change.

Current rehabilitation approaches are based on the International Classification of Functioning, disability and health (ICF) [5], describing human functioning at three different levels, i.e. ‘function’ level related to body functions and structures, ‘activity’ level related to task/skill execution and ‘participation’ level related to patients’ involvement in social life situations [6–9]. There is a growing body of evidence that training at the level of activities (e.g. task-oriented) results in improvements at both the level of body functions and the level of activity, whereas training solely at the level of body functions (e.g. isolated strength training) does not necessarily result in improvements at the level of activities [10, 11]. Furthermore, in contrast to many beliefs and dogmas in rehabilitation, persons in the chronic stage after a stroke may still have the ability to improve on arm-hand function (AHF), AHSP and actual use of the affected arm in daily life. Research has shown a 43% improvement in the amount of use of the affected arm in chronic stroke patients after an 8-week sensor-based treatment (T-TOAT) [12, 13].

#### Task-oriented arm training (TOAT)

One of the training approaches focusing on improvements on the ICF domains of activities and participation is task-oriented training [8, 14] in which the patient trains meaningful activities in a functional context [13, 15, 16]. According to theories on motor control and training physiology [17, 18], these meaningful activities may be broken down into so-called sub-activities or dominant phases (=task segmentation) and then be trained separately (=part-practise), after which the sub-activities will be ‘re-assembled’ (=chaining) towards the complete skill again [17–20].

Furthermore, feedback is essential to induce learning of motor skills. The internal feedback mechanism is often affected in stroke patients [21, 22]. Therefore, external feedback is important to gain improvements during training. One example of external feedback is haptic feedback [23, 24]. Haptic feedback is often provided by therapists using their own hands, since haptic feedback may lead to improvements on the coordination of movements and thereby also on AHSP. However, for therapists, it is nearly impossible to tailor haptic feedback towards the individual needs of the patient in a reproducible way. Research has shown that task-oriented training using the principles of motor control with sufficient practice time (repetition) may induce neuroplasticity, resulting in skill acquisition as well as retention and transfer of the newly learned skills towards similar skills (generalization), thus making learned strategies available for future behaviour [25–30].

Another advantage of task-oriented training is that the intrinsic motivation of the patient is stimulated by the use of meaningful individual person-oriented training goals related to daily living activities [31], which, in turn, is of great benefit for motor learning [32, 33] and exercise compliance [34, 35].

#### Technology-supported task-oriented arm training (T-TOAT)

In view of the high percentage of patients suffering arm-hand problems after stroke, and the limited treatment time available, new technology is being developed to assist the training of patients. Furthermore, it is well established that a high intensity of practice results in more stable improvements also after training [23]. By using technology-assisted training, AHF training and AHSP training may be augmented both in amount and duration of training as well as in content variety and task specificity. However, for a technology-assisted training to elicit significant and clinically relevant improvements of AHSP in chronic stroke patients, a combination with task-oriented training, like in the T-TOAT approach, is necessary [36]. However, evidence-based, technology-assisted training programmes for stroke patients with an Utrechtse Arm-hand Test (UAT) score [37] of 1 or 2 in the chronic phase after stroke are lacking, even though research has shown that significant improvements at function and activity level following technology-assisted treatment are possible in the chronic stage after stroke [38, 39]. The T-TOAT concept is based on principles of training physiology and motor learning, encompassing task segmentation, part-practise, chaining, overlearning, feedback, variability and training load. These ingredients make the T-TOAT concept especially suitable for training complex skills/activities by combining function level and activity level training requirements and using technology [9, 20]. Technology-assisted training may provide a challenging treatment environment, also for patients with a severely affected arm-hand, while keeping the workload for (para-)medical staff and treatment costs manageable [4, 40, 41]. However, results of previous research in the field of technology-assisted upper limb training in stroke report no or only minor improvements on either motor recovery or activities of daily living [42, 43]. A possible explanation for these findings may lay in the fact that the developed technologies are not focussing on training at the level of activities and participation [36].

#### New training approach ‘ReHab-TOAT’

A new task-oriented arm training approach using a so-called remote handling concept, to generate haptic feedback on the patient’s arm, aiming at improvements on arm function level and, ultimately, on the level of activities and participation, was developed. This approach is called ReHab-TOAT—‘Remote Handling concept based, Task-Oriented Arm Training’. ReHab-TOAT may be applicable for a wide variety of patients with arm-hand problems due to a central nervous system deficit. However, as our Rehab-TOAT approach has yet to be evaluated on its effectiveness, we chose to focus specifically on patients in the chronic stage after a stroke, since these patients, in general, receive little therapy related to impaired arm function. Also, these patients are in a more stable phase after stroke, in which spontaneous recovery is minimal. Furthermore, since ReHab-TOAT’s effectiveness has not yet been established, providing such therapy to patients in the subacute stage, thus replacing other forms of therapy, in this stage of development, is ethically unacceptable.

ReHab-TOAT uses the principles of T-TOAT in combination with assistive forces to generate enriched haptic feedback. Furthermore, ReHab-TOAT uses strategies to improve self-efficacy and self-confidence to generalize and transfer training results to different contexts.

We hypothesize that:The use of haptic feedback during task-oriented training may lead to improvements of both arm function and arm skill performance in patients in the chronic stage after a stroke suffering from a moderately to severely affected arm.The quality of life of the patient will improve.The quality of life of the caregivers will improve as a result of a reduced need to support the patient in daily life tasks.These improvements will last beyond the training phase, because patients will continue to use their affected arm in daily life more, thus creating optimal conditions for generalization and transfer of ReHab-TOAT training effects towards other daily tasks performed in different contexts.Perceived usability of ReHab-TOAT is high, since the training approach and software are developed in co-creation with therapists, physicians and patients in order to meet their needs and expectations.

### Objectives

The aim of this RCT is to investigate the effects of a 4-week ReHab-TOAT approach in addition to care as usual on improving arm function and arm-hand skill performance in chronic stroke patients with a moderately to severely affected arm-hand up to 9 months after training, compared to only care as usual. Furthermore, the aim of this study is to assess improvements in patients’ and their caregivers’ perceived quality of life, as well as the patients’ perception regarding the usability of the intervention, including both the developed approach and technology used.

## Methods: participants, interventions and outcomes

This RCT uses the SPIRIT reporting guidelines [44]. An overview of the SPIRIT checklist can be found in an Additional file.

### Study setting

This RCT will be performed at Adelante rehabilitation centre, a specialized rehabilitation clinic in the South of the Netherlands. The intervention of this RCT will be performed by a trained physical therapist or occupational therapist with experience in the treatment of patients with neurological disorders, together with a trained senior technician, all having been trained in providing the ReHab-TOAT approach.

### Recruitment and informed consent

Participants will be recruited from the electronic patient database of Adelante rehabilitation centre in Hoensbroek, the Netherlands, or via information flyers published on the website of Adelante rehabilitation centre and via a patient organization for stroke patients. Potential participants will be identified by the rehabilitation specialists of the stroke units, who will perform a preliminary eligibility screening. Potential participants reached via the website of the rehabilitation centre or the patient organization will be preliminary screened for eligibility during a phone call by a member of the research team. This will be done after the person has sent an email with his/her contact details and a declaration of interest in participation in this study. All potential eligible participants will receive an information letter with details on this study. They will be invited for a full screening by a member of the research team. During this appointment, the arm-hand function is assessed as are all inclusion criteria, and an informed consent form is signed by the patient. Similarly, the potential participant’s identified caregiver will receive a study information letter and will be asked to sign an informed consent form too, prior to his/her inclusion into the study.

### Eligibility criteria

Adult stroke patients who are currently in the chronic phase after stroke (i.e. post-stroke time longer than 12 months), who suffer from a hemiplegic arm motor impairment with an UAT score between 1 and 3 [37] and who are able to understand and execute a 3-stage verbal command are included in this study. Participants are excluded if they suffer severe non-stroke-related co-morbidity that may interfere with arm-hand function or interfering spasticity in the affected upper limb, i.e. a Modified Ashworth Scale (MAS) score >= 1+ [45].

Patients’ caregivers are included if they are over 18 years of age and provide informal care to the above-mentioned participants. Patient participants will not be excluded if their caregiver does not want to participate in this study. He/she can ask a different caregiver or decide to participate without any caregiver taking part in the study.

### Trial design and timeline

This single-blinded RCT features two arms (EXP and CONTR). The EXP group will receive a 4-week ReHab-TOAT regime additional to any care the participants may receive outside the research context. The EXP group will also receive 1 additional session to familiarize themselves with the training system, prior to the start of the training phase. The CONTR group will not receive additional arm-hand therapy apart from care as usual at this stage, i.e. therapy participants already may receive from therapists in their current home situation. In our protocol, no restrictions will be imposed on any (additional) therapies participants currently receive.

In order to assess baseline stability, baseline measurements will be taken weekly during a period of 4 weeks. For both groups, follow-up measurements will be taken after the 4-week period in which the experimental group received ReHab-TOAT, as well as 3, 6 and 9 months thereafter. Figure 1 gives an overview on intervention and measurement time points.

**Fig. 1 Fig1:**

Timeline RCT T.. time of measurement, bl baseline, fu follow-up, EXP experimental group, CONTR control group, m/mo month

### Randomization

This study will involve 30 chronic stroke patients that will be randomly allocated to either the EXP or the CONTR condition. From a logistical point of view, a maximum of eight participants can join the project at one time, i.e. in order of inclusion. This results in four sets of participants, three sets of 8 participants and one set of 6 participants. Allocation to the EXP or CONTR condition will then be randomly assigned for all participants within one set at the same time. Randomization will be performed as follows: Based on the set size, equal numbers of closed, opaque envelopes, each containing a white piece of paper containing either the acronym ‘EXP’ or ‘CONTR’, are scrambled by a researcher blinded for patient information. Subsequently, another researcher blinded for patient information will randomly draw separate envelopes from this stack, each of which will then, without having been opened, be allocated to an anonym participant code. After all envelopes within one set have been issued, the content of the opaque envelope and the participant code it was randomly allocated to will be officially recorded by the research coordinator in the presence of the latter blinded researcher. This procedure is repeated for each set of participants subsequently.

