### Statistical analysis

#### Primary study parameter(s)

Data from the primary outcome measure (FMA) will be tested for normal distribution using a Kolmogorov–Smirnov test. If normally distributed, data will be statistically analysed using a linear mixed model analysis (factors: GROUP and TIME). If, on the other hand, data are found to be skewed, a log transformation will be performed, after which a linear mixed model will be used to analyse the log-transformed data. Generally, alpha will be set at 0.05. In case of multiple comparison of the data post hoc, a Bonferroni approach will be used to avoid spurious potential false positive findings.

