#### Secondary study parameter(s)

The data from the ARAT, the MAL the EuroQol-5D and the CarerQol will be statistically analysed similarly to the data of the FMA. The data regarding patients’ amount of arm-hand use during daytime, derived from the accelerometer signals (according to the protocols described by Lemmens et al. [66] and Franck et al. [38]), will also be statistically analysed similarly to the procedure used to analyse differences in the data of the FMA. Results from the SUS and the questionnaire on user experience of technology used will be reported descriptively. The single questions gauging for any event that may have influenced the patient’s or caregiver’s answer or measurement will only be used to identify/interpret any unexpected measurement and will be reported descriptively. The frequency and content of any additional therapy the participants received during the intervention period will be also reported.

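### Allocation is balanced within four sets but the stated model has only GROUP and TIME, so any between-set variation in the tested contrast stays in the error term: a minor loss of efficiency

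*Protocol article*

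**What the plan says.** **Design.** Under Randomization, sets are filled by order of inclusion because "a maximum of eight participants can join the project at one time, i.e. in order of inclusion". The section then states: "This results in four sets of participants, three sets of 8 participants and one set of 6 participants". Each set is allocated on its own: "Allocation to the EXP or CONTR condition will then be randomly assigned for all participants within one set at the same time". The stack for each set is balanced ("Based on the set size, equal numbers of closed, opaque envelopes" for the two conditions), and the procedure is repeated for every set.

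**Analysis.** Under Primary study parameter(s), FMA is analysed, on the original or the log scale, with a "linear mixed model analysis (factors: GROUP and TIME" as its only named factors. Under Secondary study parameter(s), ARAT, MAL, EuroQol-5D and CarerQol "will be statistically analysed similarly to the data of the FMA", and accelerometry follows the same procedure. The protocol article names no set, block or cohort term in any model, and it gives no figure for variation between sets.

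**The concern.** The analysis would normally reflect the restriction placed on the randomisation. Here the restriction is set, and set is not among the listed factors.

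Sets could differ in ways that bear on the outcomes. At most eight participants join at one time, and Trial status gives recruitment from January to October 2022, so sets enter at different points of the year. The training is tailored continuously, and the therapists meet regularly to discuss it (Intervention), so delivery may develop over time. Usual care is unrestricted (Trial design and timeline). A single assessor removes inter-observer differences but not drift. These are plausible sources of variation; the documents do not show that they operate.

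What is at stake is precision. If sets differ in the contrast being tested, the reported intervals are wider than the design warrants and some power is given away in a trial of 30 patients.

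**Working it through.** **1. The plan's own figure.** Sample size gives log FMA 1.47 (SD 0.12) before and 1.65 (SD 0.11) after, two-sided alpha 0.01, power 0.90 and 10% loss.

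- Difference = 1.65 − 1.47 = 0.18; pooled variance = (0.0144 + 0.0121)/2 = 0.01325.
- n = 2 × 0.01325 × (2.576 + 1.282)² / 0.18² = 12.2, so 13 per arm; 13/0.9 = 14.4, so 15 per arm.

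This matches the stated 15 per group. The point below does not alter it.

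**2. Balance.** 3 × 8 + 6 = 30 patients. Equal envelopes give 4:4, 4:4, 4:4 and 3:3, and 3 × 4 + 3 = 15 per arm, which agrees with the stated group size. A shift common to a whole set therefore cancels from EXP minus CONTR.

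**3. What stays in the error term (comparison of levels).** Let ρ be the share of total variance lying between sets (assumed, since the documents give none). Without a set term there are 28 residual degrees of freedom. The multiplier of the between-set variance in the residual sum of squares is 30 − (8² + 8² + 8² + 6²)/30 = 30 − 228/30 = 22.4. The residual variance thus picks up 22.4/28 = 0.80 of the between-set variance, and

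model SE / true SE = √[(1 − ρ + 0.80ρ)/(1 − ρ)] = √[(1 − 0.20ρ)/(1 − ρ)].

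For example, at ρ = 0.10: √(0.98/0.90) = 1.04.

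**4. Simulation.** 20,000 trials per scenario, sets of 8/8/8/6, all 30 analysed, an illustrative effect of 1 SD for power, and the analysis level from the protocol article ("Generally, alpha will be set at 0.05"):

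| ρ (assumed) | SE ratio without set | Type I error, without / with set | Power, without / with set |
|---|---|---|---|
| 0 | 1.00 | 0.049 / 0.049 | 75.0% / 74.9% |
| 0.05 | 1.02 | 0.046 / 0.051 | 76.5% / 77.5% |
| 0.10 | 1.04 | 0.040 / 0.048 | 76.6% / 79.1% |
| 0.20 | 1.10 | 0.032 / 0.048 | 79.3% / 84.1% |
| 0.30 | 1.16 | 0.029 / 0.050 | 80.5% / 88.1% |

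A four-level set term takes the residual degrees of freedom from 28 to 25 and the critical t from 2.048 to 2.060.

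**5. Change from baseline.** Take one post-intervention value minus the mean of four baselines, with an assumed residual variance of 0.2 against a between-patient variance of 1. The variance of change is 0.2 + 0.2/4 = 0.25, and SE = √(0.25 × 2/15) = 0.183.

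- Sets hold 30% of the variance in level and none in change: SE 0.1825 without set, 0.1824 with set. Nothing is gained.
- Sets hold 10% of the variance in change: SE 0.190 against 0.183; type I error 0.041 against 0.049.
- Sets hold 20% of the variance in change: SE 0.200 against 0.183; type I error 0.036 against 0.049.

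**6. Which set term acts.** A SET main effect is the same at every time point, so it drops out of a within-patient GROUP by TIME contrast; SET by TIME is needed there. With four sets this adds (4 − 1) × (8 − 1) = 21 parameters for FMA, ARAT and MAL at all eight time points in Table 2. It adds (4 − 1) × (5 − 1) = 12 for outcomes with one baseline and four follow-ups, and (4 − 1) × (2 − 1) = 3 with TIME reduced to pre/post.

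**The case against.** The strongest objection is that the treatment effect is a within-patient change. Objectives speaks of improvement, Methodological considerations of change relative to baseline, and FMA is measured four times before and four times after the intervention. Under that contrast, stable set differences in level, including most differences in case mix, cancel within patient. This stands. It limits the concern to set differences in change, and it means that simply adding a SET main effect to the stated repeated-measures model would recover nothing for GROUP by TIME. The protocol article names neither the interaction nor the random effects, so it does not settle which contrast applies.

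Next, the between-set share may be small: one centre, one assessor, chronic patients described as stable, and sets formed for logistics and not on a prognostic factor. Each patient is followed for about 11 months (two 4-week periods plus 9 months), so the sets' measurement periods can overlap considerably. This also stands, and at a share of zero nothing is lost.

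Finally, an article condenses the full plan, and an analysis plan that is not shown might add set. If it does, the point is closed. But the article lists the factors by name, and set is not one of them.

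A reader might infer that the omission biases the comparison or makes the test invalid. It does neither: balance removes set from the estimate, and the error is in the conservative direction. A reader might also apply 1/√(1 − ρ), giving 2.6%, 5.4% and 11.8% for shares of 5%, 10% and 20%. That would hold only if all the between-set variance entered the residual; with these set sizes 0.80 of it does.

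**Conclusion.** The point holds as a minor efficiency improvement. The protocol article blocks on set and states a model without it. Any between-set variation in the analysed contrast therefore inflates the standard error and makes the test somewhat conservative.

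The size cannot be fixed from the documents. For a level contrast, the standard error is about 2%, 4% or 10% too large at assumed between-set shares of 5%, 10% or 20%, with power differences of about 1, 2.5 and 5 points for the illustrative 1 SD effect. For change from baseline, similar percentages apply only to the share of variance in change. The figures assume that all 30 patients are analysed, so that balance within sets is exact; dropout, or caregivers who do not take part, would make it approximate. The documents do not support saying that the standard error is inflated as a matter of fact, because no between-set variance is reported.

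**What to change.** Include SET (four levels) in the models for FMA, ARAT, MAL, EuroQol-5D, CarerQol and accelerometry, in a form that acts on the tested contrast:

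- **Baseline as covariate:** model the post-intervention values adjusted for baseline, with a SET term (3 degrees of freedom).
- **Baseline in the outcome vector:** add SET and SET by TIME, preferably with TIME reduced to pre/post, so that the interaction costs 3 parameters and not 21 (FMA, ARAT, MAL) or 12 (the others).

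State which of the two is used, and name the contrast that carries the treatment effect. The System Usability Scale and the user-experience questionnaire are reported descriptively and need no change.

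The cost is a few degrees of freedom: for 3, the critical t moves from about 2.048 to 2.060, and with no set effect the simulated power is 74.9% against 75.0%. The sample size stays at 30 and no new data are needed, since set membership is known from the allocation procedure.
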